### Intervention

All students will receive the Thriving Minds program, either after the first survey (intervention condition), or after the third survey (wait-list control condition). The Thriving Minds program is conducted over two 50-minute sessions, delivered one week apart. The program aims to address mental health literacy and stigma by normalising uncomfortable emotional experiences, equipping students with effective self-care strategies, and encouraging them to seek help for emotional problems. Content is mapped to the Australian curriculum and delivered with classroom teachers present, who are ideally placed to support ongoing classroom use of emotion literacy content [27]. The program sessions focus on key concerns for 8–10-year-olds, including coping with stress/anxiety and low mood. The content is delivered through developmentally appropriate story books relating to anxiety and depression and classroom discussions and activities relating to the development of emotion literacy. Specifically, content focuses on recognition of emotional experiences (identification of different emotion characteristics, including physiological characteristics, distinguishing between comfortable and uncomfortable and big and small emotions), knowledge about appropriate regulation actions (self-care strategies), and help-seeking for uncomfortable emotions. A summary of the program content is included in the Supplementary Materials A.

**Fig. 1 Fig1:**
[figure not shown]
Flow of participants

### Patient and public involvement

Thriving Minds was developed by MIEACT in response to feedback from schools indicating a gap in mental health literacy education for 8-10-year-old children. School teachers were consulted in the design of the program and provided feedback in the uncontrolled post-program evaluation to improve the design. For the current evaluation, prior to the commencement of the trial, a sample of 8–10 year-old children trialled the measures. Adjustments were made based on their responses to improve clarity and comprehension. School education directorates assessed and approved the burden of the intervention and time required to participate in the research and approved measures. Schools will be provided with study summary findings to disseminate to their communities.

### Measures

Table 1 presents the proposed measures that will be administered to children, teachers, and parents at each measurement occasion in the Thriving Minds trial. Some measures are existing validated measures that have been adapted for developmental literacy levels as indicated, and other measures were developed specifically for the study where no existing validated measures were available for children.

#### Help-seeking

The primary outcome for the current trial is *Help-seeking intentions* and will be assessed using the General Help-Seeking Questionnaire [GHSQ] [28]. Participants will be asked to rate how likely they are to seek help for big uncomfortable emotions from a range of people, including a friend, teacher, parent, family member, psychologist or school counsellor, doctor, and Kids Helpline (phone helpline). Participants will be provided with the opportunity to nominate another person (‘Other’) if they want to. All items will be responded to on a 5-point scale ranging from 1 (Extremely unlikely) to 5 (Extremely likely). Participant *help-seeking knowledge* will be measured by asking children to provide a free text response to indicate who they would get help from if they were having uncomfortable emotions (adapted to an open-ended question from a multi-choice response item on the GHSQ [28]). Total informal (e.g., family, friends, teacher) and formal (e.g., GP, psychologist, helpline) sources of help will be calculated.

Participant *help-seeking confidence* will be measured with a single item asking children to indicate on a 5-point scale ranging from 0 (Not at all) to 4 (Extremely) how easy it is for them to seek help. This item is adapted from a previous study [29], with the term ‘easy’ replacing ‘confidence’ to align with developmental literacy levels.

Participant *help-seeking attitudes* will be measured by asking children to rate how helpful each of 12 actions are for when they have *big, uncomfortable emotions*, using a 5-point rating scale ranging from 1 (very unhelpful) to 5 (very helpful), adapted from [30]. The list includes *no action* options (e.g., ‘Pretend the emotions aren’t there’), *self-help* actions aligning with the content of the Thriving Minds program (e.g., ‘Do something to make myself feel better (self-care)’), *informal help-seeking* actions (e.g., ‘Talk to a parent’) and *formal help-seeking* actions (e.g., ‘Talk to a psychologist or school counsellor’). Each individual response item will receive a helpfulness rating, and average scores across no action, self-help, informal help-seeking and formal help-seeking will also be calculated.

*Actual Help-Seeking and Self-Help Behaviours* will be measured using an adapted version of the Actual Help-Seeking Questionnaire (AHSQ) [31]. The list of response options will be the same as the *attitudes to help-seeking* question (see above), with participants endorsing the sources/activities they have engaged with. Total ‘no action’, ‘self-help’, *‘*informal help-seeking’, and ‘formal help-seeking’ scores will be calculated.

#### Emotion Knowledge

Participants will demonstrate their *emotion vocabulary* by making a list of comfortable and uncomfortable emotions (similar to [32, 33]). The total number of emotions that participants list and correctly categorise as comfortable and uncomfortable will be counted.

Participant *emotion recognition* will be measured using three vignettes about children having uncomfortable emotional experiences that were developed to align with content covered in the Thriving Minds program (exclusion from a birthday party, missing out on a favourite breakfast cereal, and worry about an upcoming school carnival). Children will be asked to identify the emotion(s) that they think the character is feeling from a list of 12 emotions (frustrated, worried, depressed, relieved, happy, sad, relaxed, angry, anxious, bored, disappointed, scared). Children will also be asked to identify if the character’s emotion is comfortable, uncomfortable, or not sure, and big, small, or not sure. Total appropriate, potentially appropriate, and inappropriate emotions will be coded and calculated for each vignette, and average scores across the three vignettes will also be calculated. Average accuracy of identification of comfort and size of emotions will also be calculated.

Participants will be asked about their knowledge of the *physiological components of emotions* by indicating “which feelings occur in the body when someone is feeling sad/happy/worried?” Children will be able to select one or more options from a list of 13 options (e.g., Hot, Calm, Beating Heart). ‘Not sure’ and ‘Other’ options will also be available. The question was developed to align with Thriving Minds content. Total appropriate, potentially appropriate, and inappropriate physiological components will be coded and calculated for each vignette, and average scores across the three vignettes will also be calculated.

Participant *bodily awareness of emotions* will be measured using the 5 items of the Bodily Awareness sub-scale of the Emotion Awareness Questionnaire [EAQ], α = 0.64 [34]. Each item has a 3-point response scale ranging from 1 (Not true) to 3 (True). A mean sub-scale score will be calculated across items, with scores ranging from 6 to 18. Items are reverse coded (except one) so that higher scores reflect lower bodily awareness.

#### Emotion attitudes

Children’s *emotion attitudes* will be measured using the 5 items of the Not Hiding Emotions subscale of the EAQ, α = 0.68 [34]. Each item has a 3-point response scale ranging from 1 (Not true) to 3 (True). All items are reverse scored. A mean sub-scale score will be calculated across items, with scores ranging from 6 to 18. Higher scores reflect less hiding of emotions.

#### Stigma

Participants will be provided with two vignettes, one about worry, and one about sadness, adapted for developmental appropriateness (less text, simpler language) from vignettes about anxiety and depression that have been used in prior research with adolescents [35]. *Stigma attributions*, or negative judgement pertaining to children who experience uncomfortable emotions, will be measured by asking participants to indicate how much they agree or disagree with six statements about each vignette character, using a 7-point scale ranging from 1 (Strongly disagree) to 7 (Strongly agree). All items were adapted from the Revised Attribution Questionnaire [r-AQ], α = 0.68 [36, 37]. A total stigma attribution score will also be calculated by summing the item scores. Total scale scores can range from 6 to 42, with higher scores indicative of higher stigmatising attitudes. An additional item (“I would not want to be friends with [character]”) was also added to the scale, adapted from [35], which will be analysed individually.

Emotion stigma will also be measured by asking participants to complete a *stigma association* task adapted for developmental appropriateness (less options, simpler language) from the Stigma of Suicide Scale Short Form (SOSS-SF) [38]. Participants will be provided with the statement “people who have big feelings are” and ask them to rate using a 5-point scale ranging from 1 (Strongly disagree) to 5 (Strongly agree) their level of agreement with a list of 15 descriptors (e.g., attention-seeking, brave, embarrassing, hurtful to others, lazy). Items load onto 3 subscales (Stigma, α = 0.88; Isolation/depression, α = 0.80; Normalisation/glorification, α = 0.78). Mean subscale scores will be calculated, ranging from 1 to 5. Higher scores reflect higher levels of stigma, greater attribution to isolation/depression or greater normalisation/glorification.

#### School support

School support will be measured using two scales originally from the Sources of Strength trials [39, 40], adapted with minor language modifications. Four items will be used to assess *peer integration* at school, addressing both inclusion and isolation. Participants will respond to each item on a 4-point scale ranging from 1 (Strongly disagree) to 4 (Strongly agree). A mean scale score is calculated. Higher scores reflect higher peer integration. *Trusted adults at school* will be measured using a 4-item scale, α = 0.90 [41] on which participants rate their connections to adults at school on a 4-point scale ranging from 1 (strongly disagree) to 4 (strongly agree). A mean scale score is calculated, with higher scores indicative of students having adults at school that they feel they can trust and talk to about problems.

#### Wellbeing

Using the Stirling Children’s Wellbeing Scale (excluding the 4 lie-scale items) [42], participants will be asked to rate 12 statements about their mood, levels of enjoyment, and positive expectations in life, using a 5-point scale ranging from 1 (Never) to 5 (All the time), α = 0.82. Total scale scores are calculated by summing item scores, with total scale scores ranging from 12 to 60. Higher scores are reflective of greater emotional wellbeing.

#### Demographic and study characteristics

In the pre-intervention survey, all participants will be asked to provide their age (7, 8, 9, or 10 years) and gender (boy, girl, don’t feel like a boy or girl). At post-intervention, participants in the intervention condition will be asked to indicate the number of Thriving Minds sessions they completed (0, 1, 2, unsure). At the time of consent, parents will be asked to indicate if the participating child speaks more than one language, and if the child has a diagnosis of autism, attention-deficit/ hyperactivity disorder (ADHD), learning difficulties, depression, anxiety, or another mental health condition. Parents can elect not to complete these items. School decile ratings will be used to provide an indication of socio-economic status.

#### Acceptability and Satisfaction

Program acceptability and satisfaction will be assessed in intervention condition schools, at post-intervention using a 3-item bespoke measure and open-ended questions assessing what participants liked most and least about the program and what they found to be most helpful.

### Teacher survey

Usual classroom teachers at intervention schools will be asked to complete a brief survey at the post-intervention and 12-week follow-up timepoints. At each time-point, teachers will be asked to rate the extent to which they agree with nine statements regarding perceived value of program content, intention to use content, and actual use of content, using a 5-point scale ranging from 1 (Strongly disagree) to 5 (Strongly agree). A sixth response option, ‘NA/not sure’, will also be available. Teachers will also be asked four open-text response questions identifying what they liked most and least about the Thriving Minds program, possible program improvements, and if they had completed any follow-up activities relating to Thriving Minds content.

### Focus groups and interviews

Two groups of 4–5 children from 3 to 4 intervention condition schools will be invited to take part in focus groups to further explore the value, strengths and weakness of the Thriving Minds program. Using open-ended prompts, children will be asked to discuss what they learned from the program, its strengths and weaknesses, how ideas from the program have been used in the classroom or school environment, what they told their parents about the program, and what they would tell a peer about the program.

Semi-structured interviews will also be conducted with teachers and executive staff responsible for student wellbeing in intervention condition schools at 12-week follow-up.

**Table 1 Tab1:** Intervention and measures timeline

	Study Period				
	Pre-intervention	Intervention	Post-intervention	12-week follow-up	Post 12 week follow-up
**Interventions**					
Intervention					
Waitlist Control					
***Child Measures***					
**Demographic Characteristics**					
Age	✓		✓	✓	
Gender	✓		✓	✓	
Languages spoken (parent reported)	✓				
Mental health diagnosis (parent reported)	✓				
**Help-seeking Measures**					
Help-seeking knowledge, Adapted GHSQ [13]	✓		✓	✓	
Help-seeking intentions, GHSQ [28]	✓		✓	✓	
Help-seeking confidence [29]	✓		✓	✓	
Help-seeking attitudes, adapted from [30]	✓		✓	✓	
Actual self-help behaviours, Adapted AHSQ [31]	✓		✓	✓	
**Emotion Knowledge**					
Emotion Vocabulary, bespoke measures adapted from [32, 33]	✓		✓	✓	
Emotion Recognition (bespoke measure)	✓		✓	✓	
Physiological components (bespoke measure)	✓		✓	✓	
Bodily Awareness: EAQ subscale [34]	✓		✓	✓	
**Emotion Attitudes**					
Not Hiding Emotions: EAQ subscale [34]	✓		✓	✓	
**Stigma**					
Emotion stigma: Vignette rating scale, adapted from [35–37]	✓		✓	✓	
Emotion Stigma: Adapted SOSS [38]	✓		✓	✓	
**School support**					
Trusted adults at school [39, 41]	✓		✓	✓	
Peer integration at school [39]	✓		✓	✓	
**Wellbeing**					
Stirling Children’s Wellbeing Scale [42]	✓		✓	✓	
**Acceptability and Satisfaction**					
Acceptability and Satisfaction (bespoke measure)			✓	✓	
***Teacher Measures***					
Perceived value, intention to use, actual use (bespoke survey measure)			✓	✓	
***Qualitative measures***					
Staff interviews				✓	
Child focus groups				✓	

Teachers will be asked to share their perspectives on the program, including its acceptability, overall satisfaction with program content, and any observed changes in student behaviour and/or school culture that may have occurred as a result of the Thriving Minds program.

### Data analysis plan

Written survey data will be entered verbatim into Qualtrics by researchers who are blind to participant condition. All research data will be securely stored at the Australian National University for at least five years from the date of any publication arising from the research and will be accessible to members of the research team. At the end of the five-year period, electronic survey and transcription data will be archived in a deidentified format (all reasonably identifying information removed) and may be shared with other researchers, with permission from the original research team.

Analyses of continuous measures will be undertaken on an intention-to-treat basis, including all participants allocated regardless of treatment actually received or withdrawal from assessments. Mixed-model repeated measures (MMRM) analyses will be used because of the ability of this approach to include participants with missing data. In addition, by incorporating appropriate random effects for each school, MMRM will accommodate and assess the strength and significance of clustering effects. MMRM is the standard and most robust methodology for analysing cluster randomised trials [43, 44]. Using (MMRM) ANOVA models, measurement occasion will be included as the within-group factor and condition as the between-groups factor [45]. For any dichotomous outcomes, a comparable binary mixed modelling approach [46] will be used. Cohen’s *d* effect sizes will be calculated for primary and secondary outcomes at each time-point. If efficacy is demonstrated, exploration of potential mediators and moderators of response, such as child age, child mental health, baseline emotion literacy, participant gender and intervention completion, will be explored separately using 3-way interaction terms subgroup analyses.

Qualitative analysis of the semi-structured interviews will be conducted using Framework Analysis. Framework Analysis was designed for addressing social policy research questions [47] and has been used frequently in health research [48]. It follows a systematic process of inductive coding, generating a table of findings across participants that is conducive to interpretation and input from multiple researchers.

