### Aims and hypotheses

Using a pragmatic cluster-controlled trial, this study will investigate the efficacy of a school-based mental health literacy program for 8-10-year-old children. The primary aim of the trial is to evaluate the effect of the Thriving Minds program on help-seeking intentions for uncomfortable emotions at post-intervention (and, secondarily, 12-week follow-up), compared to the wait-list control condition. It is hypothesised that participants receiving the Thriving Minds program, relative to participants in the wait-list control condition, will report higher levels of help-seeking intentions for uncomfortable emotions at post-intervention.

The secondary aims are to evaluate at post-test and 12 week follow-up the following: 1) the efficacy of Thriving Minds on a range of help-seeking outcomes: (a) help-seeking confidence, b) help-seeking knowledge, c) help-seeking attitudes, d) actual self-care behaviours, and e) actual help-seeking behaviours; 2) the effect of Thriving Minds on emotion knowledge ((a) emotion recognition and (b) physiological components of emotion); and 3) the effect of Thriving Minds on stigma. It is hypothesised that participants receiving Thriving Minds will report improvements in each of these outcomes relative to the waitlist control.

Exploratory aims include exploring *Predictors and mediators* of intervention effects, including demographic characteristics, mental health conditions, emotion knowledge (emotion vocabulary, and bodily awareness of emotions) and emotion stigma (emotion attitudes (not hiding emotions)), wellbeing, and school support. These analyses will also investigate subgroup effects, such as whether the Thriving Minds program has a greater effect on emotion knowledge among students with low pre-existing knowledge.

A final aim of the study is to conduct a qualitative evaluation to assess *student and staff satisfaction* with the program, including what students liked and learned in the program, any suggested improvements, and any observable changes in student learning, behaviour or wellbeing following the intervention.

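### The 3-way interactions planned for mediators and moderators suit the baseline moderators, but they do not test mediation and cannot be estimated for intervention completion

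*Protocol article*

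**What the plan says.** The protocol's Data analysis plan fits a mixed model for repeated measures in which "measurement occasion will be included as the within-group factor and condition as the between-groups factor". Once efficacy has been shown, it adds "exploration of potential mediators and moderators of response". The examples are child age and four others: "child mental health, baseline emotion literacy, participant gender and intervention completion, will be explored separately using 3-way interaction terms subgroup analyses". No other method for mediators is named.

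Under Aims and hypotheses, predictors and mediators form an exploratory aim, given as a single list "of intervention effects, including demographic characteristics, mental health conditions, emotion knowledge" and further constructs such as emotion attitudes, wellbeing and school support. The list does not separate predictors from mediators.

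Completion is defined under Demographic and study characteristics: "At post-intervention, participants in the intervention condition will be asked to indicate the number of Thriving Minds sessions they completed (0, 1, 2, unsure"). The Intervention section says that wait-list children receive the program only after the third survey.

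**The concern.** One sentence covers three kinds of variable that need different analyses.

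- **Baseline characteristics** (age, gender, mental health, baseline emotion literacy). An occasion × condition × covariate term is the normal test of whether the effect differs by their level.
- **Mediators.** The question is whether the program changes the mediator and whether that change carries through to help-seeking intentions. An interaction term does not estimate that quantity.
- **Completion.** This arises after allocation and varies only in the intervention arm, so its interaction with condition has nothing to compare.

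If the sentence is followed literally, an interaction could be reported as evidence for or against mediation. For completion, the software would drop columns or fail, and the analyst would have to choose a replacement after seeing the data.

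**Working it through.** The plan states no figure to reproduce here. The check concerns model structure.

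**Inputs from the protocol.** Three occasions; the base model of occasion by condition; sessions recorded as 0, 1, 2 or unsure in the intervention arm only; no control sessions before the last survey; about 500 children.

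**Assumptions.** 250 children per arm (500 / 2), and attendance of 5%, 15% and 80% for 0, 1 and 2 sessions. The ranks below do not depend on these shares as long as all three values occur.

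**Step 1: the completion term.** Let C be condition, S sessions, and T1 and T2 the two later occasions. With S numeric, the fixed effects are {1, C, S, C×S} each crossed with {1, T1, T2}, so 4 × 3 = 12 columns.

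- *Controls coded 0.* S = 0 whenever C = 0, so C×S = S in every row. Three distinct blocks remain, {1, C, S}, and the rank is 3 × 3 = 9. The lost columns are C×S, C×S×T1 and C×S×T2. The last two are the 3-way term.
- *Controls missing.* Rows without the covariate drop out, so C = 1 throughout. C duplicates the intercept and C×S duplicates S. The rank is 2 × 3 = 6, and condition itself is lost.
- *Sessions as categories.* There are 2 × 3 × 3 = 18 columns. With controls at 0 the blocks are {1, C, S1, S2}, giving rank 4 × 3 = 12. With controls missing they are {1, S1, S2}, giving rank 3 × 3 = 9.

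| Coding | Columns | Rank | 3-way term estimable? |
|---|---|---|---|
| Numeric, controls 0 | 12 | 9 | No |
| Numeric, controls missing | 12 | 6 | No |
| Categorical, controls 0 | 18 | 12 | No |
| Categorical, controls missing | 18 | 9 | No |
| Hypothetical: sessions vary in both arms | 12 | 12 | Yes |

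Numerical rank calculations gave these same values. With controls at 0, the occasion × S columns survive. They compare change between intervention children who attended different numbers of sessions.

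**Step 2: mediation against interaction.** The simulation had 200,000 children and a single post-baseline outcome Y, so the 3-way term reduces to C×M for a mediator M.

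- *Full mediation, no interaction:* M = 0.5·C + error and Y = 0.7·M + error. The true indirect effect is 0.5 × 0.7 = 0.35. The fitted C×M coefficient was −0.006.
- *Interaction, no mediation:* M is unrelated to C, and Y = 0.35·C + 0.3·C×M + error. The fitted path from C to M was −0.003, and the fitted C×M coefficient was 0.296.

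The interaction missed mediation that was complete, and it was clearly positive where there was none.

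**Step 3: the subgroup reading.** Completers can be compared with all controls, and that contrast is estimable. But completers are selected by something that happens after allocation, and no matching subset of controls can be identified. The contrast therefore mixes the program's effect with whatever leads a child to attend both sessions.

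**The case against.** **The sentence is ambiguous.** It lacks a conjunction and may mean interaction terms or subgroup analyses, and the Aims section does mention subgroup effects. This stands: non-estimability applies to the 3-way term and not to every analysis of completion. The subgroup route is confounded, however, and it does not test mediation either.

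**An article may leave the mediation model to the analysis plan.** That would answer a complaint that detail is missing. Here a method is stated and attached to mediators, and it is the wrong one. It is fair to add that four of the five examples are proper baseline moderators.

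**The reach is small.** This stands. The aim is exploratory and is pursued only after efficacy is shown.

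A reader might infer more than the protocol supports:

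- *That the data hold nothing usable on completion because controls have no values.* Control exposure during follow-up is known to be zero, and the occasion × sessions contrast in the intervention arm remains estimable.
- *That completion is nearly the same variable as condition.* The exact duplication is between condition × sessions and sessions. Sessions and condition stay distinct as long as attendance varies.
- *That mediation cannot be studied in this trial.* Emotion vocabulary, bodily awareness, emotion attitudes and stigma are all scheduled at all three occasions in Table 1.

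**Conclusion.** The stated method fails for two of the things it covers. A 3-way interaction does not estimate an indirect effect, whatever the sample size. The completion term is not identified under any of the codings examined: rank is 9 or 6 for 12 columns with numeric sessions, and 12 or 9 for 18 with categorical sessions. This rests only on sessions being confined to the intervention arm before the last survey, which the protocol states. For age, gender, mental health and baseline emotion literacy the method is appropriate and should stay.

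The consequence is limited to the exploratory analyses. The primary and secondary comparisons do not use this model and are unaffected.

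**What to change.** Split the sentence in the Data analysis plan into three.

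1. **Baseline moderators.** Keep the occasion × condition × covariate terms for age, gender, mental health and baseline emotion literacy only.
2. **Completion.** Remove it from that list. Report an adjusted dose-response by number of sessions within intervention schools, state how answers of unsure are handled, and label the result non-causal.
3. **Mediators.** Name the candidates and fit a separate indirect-effect model: the post-intervention mediator predicting 12-week intentions, adjusted for baseline mediator and baseline intentions. Account for school clustering by a method suited to about 12 schools. Resampling whole schools, six per arm, is too coarse for dependable intervals. Label the result exploratory and non-causal, because allocation is not random and mediators are not randomised.

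The mediator model puts the mediator before the outcome in time, so it addresses intentions at 12 weeks and not the primary time point at post-intervention. The text should say so.

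The cost is a change of wording and modest extra programming, with no new data. The downside is that indirect-effect intervals will be imprecise with so few schools.
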